## Abstract

**Background:**

Despite the wealth of evidence demonstrating the health benefits of physical activity (PA), people with arthritis commonly do not meet recommended PA levels. Whilst various programmes support people with arthritis to become active, most individuals reduce their level of PA after completion of a structured exercise programme. This research aims to co-develop and feasibility test a PA maintenance intervention for those living with arthritis, after exit from a structured exercise programme.

**Methods:**

Intervention development was guided by the INDEX framework for developing complex interventions.

Phase 1, Evidence Synthesis: Bring together existing evidence, clinical guidelines and behavior change theories for PA maintenance in arthritis, to develop an intervention logic model.

Phase 2, Observation and qualitative study: Conduct an observational analysis of a physiotherapy led structured exercise programme for those living with arthritis, to understand what behaviour change components are used and what might support PA maintenance. Followed by a qualitative exploration of PA maintenance barriers, facilitators and strategies for those who have participated in the classes, their family members/friends and the delivering physiotherapist.

Phase 3, Finalise intervention prototype: Results from phases 1 and 2, will be triangulated to inform potential intervention options. Those living with arthritis/key stakeholders will be invited to participatory workshops to refine intervention content and delivery modes.

Phase 4, Feasibility Study: The final phase is a pre-post, mixed methods feasibility evaluation of the newly developed multicomponent PA maintenance intervention for people living with arthritis, after completion of a physiotherapy led structured exercise programme.

**Discussion:**

Intervention development will bring together PA maintenance theory and evidence with user input and other key contextual factors. User input will be achieved by collaboration with two embedded patient researchers and a wider Public Patient Involvement (PPI) panel to ensure diverse patient experiences and perspectives are heard and inform programme design.

## Introduction

There is a wealth of evidence that physical activity (PA) protects health across the life course, especially for those living with chronic health conditions. Despite this, insufficient amounts of PA remain one of the major behavioural challenges worldwide
^
1
^. Many Irish adults are not meeting the PA guidelines
^
2
^, and those living with health conditions such arthritis, are even more likely to be inactive. This places them at risk of developing further health conditions and exacerbating their need for rehabilitation
^
3
^.

### Physical activity and its benefits

Physical activity is defined as any movement produced by skeletal muscles resulting in energy expenditure, and includes all PA done as part of daily living such as social and domestic activities, commuting, recreational and leisure activities
^
4–
7
^. PA is consistently recommended in arthritis management guidelines with moderate evidence of benefits on cardiovascular fitness, muscle strength, pain management and disability on completion of interventions
^
8,
9
^. PA interventions also show short-term effectiveness in supporting people to be active
^
10
^. However, there is no evidence for the long-term maintenance of PA.

### Programmes to support increases in PA

Strategies to support people with arthritis to be active include health service or third sector exercise programmes delivered in person and increasingly virtually, since the COVID-19 pandemic
^
10,
11
^. Many individuals reduce their level of PA after completion of a prescribed programme
^
8,
12,
13
^. It is well established that maintenance is critical to sustain clinical benefits of exercise programmes and protect long-term health
^
8,
14
^. One reason for this decline in activity level may be that interventions designed to support the initiation of PA (e.g. supervised exercise programmes) typically cease without planned contact and follow-up activities. Further, the programmes generally lack the necessary behaviour change components for PA maintenance, such as becoming autonomous and creating new habits
^
15
^. They typically also neglect to take into account those factors that people find enjoyable or satisfying, such as social contact and enjoyment of activities. These are known to be important for maintenance, particularly in older and more socially isolated people
^
16,
17
^, and therefore should be taken into account when developing long-term PA maintenance interventions
^
17
^.

### Physical Activity maintenance

Though there is no consensus on how to define PA maintenance
^
18–
21
^. the most widely accepted conceptual definition is a period of sustained behavioural engagement above a threshold that improves health and well-being. Maintenance is achieved following initial adoption of the behaviour and is observable e.g., meeting aspects of the physical activity guidelines
^
19
^. In contrast to such concrete observable behaviour it has been argued by others that physical activity maintenance is instead a process marked by a shift in the mechanisms of action determining the behaviour from those used for initiation compared to those used for maintenance e.g. a shift from slow effortful conscious to non-conscious automatic processes driving behaviour
^
19,
20
^. Operational definitions of physical activity maintenance have commonly focused on the former conceptual definition of observable behaviour above a specific threshold after the original intervention ends, e.g., three to 12 months following the end of an exercise programme
^
12
^. In previous scoping and systematic reviews, we have included studies with a follow up time point of at least three months after intervention end
^
12,
22
^.

### Starting to become active

Evidence suggests that for PA interventions to be effective, they should be informed by behaviour change theory which supports people to incorporate PA into their daily life
^
23
^ (synthesis of 100 reviews). Emerging evidence also suggests that this applies to people living with arthritis. A meta-analysis of 11 randomised controlled trials (RCTs) of counselling-based PA interventions demonstrated small increases in PA levels
^
8
^. The European League Against Rheumatism (EULAR) 2018 guidelines for the first time, now specifically recommend PA as an integral part of standard management; acting as a bridge between arthritis-specific exercises and public health PA recommendations
^
14
^.

### Existing maintenance programmes

In arthritis, there is some evidence to support behaviour change approaches delivered digitally
^
8,
24,
25
^ and non-digitally
^
8,
9,
14
^ to initiate PA behaviour. A range of booster strategies have been reported such as phone calls, devices, home visits, logbooks, web-based instructions, written material and visual instructions
^
8
^. However, even with such behaviour change support their effectiveness regresses to previous levels once the intervention is completed
^
26
^. This means we know very little about how to support people to maintain PA behaviour long-term. Existing literature in this area demonstrates a lack of reporting of maintenance outcomes, small improvements at follow-up that often diminish over time or no significant differences in PA maintenance outcomes
^
27,
28
^. Another study reported on the feasibility of a maintenance intervention for older adults following a falls programme
^
29
^. The intervention was feasible and a small increase in PA was identified in both intervention and control groups at 6-months follow-up. The intervention was, however, not designed for people with arthritis and the theoretical underpinning was unclear.

The overall aim of this piece of research is:

To co-develop and feasibility test a PA maintenance intervention for those living with arthritis after exit from a physiotherapy led structured exercise programme. Intervention development will be informed by four study phases that are guided by the MRC framework
^
30
^, and IdentifyiNg and assessing different approaches to DEveloping compleX interventions framework (the INDEX study)
^
31–
33
^. 

This aim will be achieved through five objectives, conducted over four study phases

(i) Synthesis of PA maintenance theory and evidence(ii) Identify facilitators/deficits in supervised exercise classes to maintain PA(iii) Identify the support needs of people living with arthritis, their family members/friends and the delivering physiotherapists, to maintain PA.(iv) Co-develop a PA maintenance intervention prototype(v) Test the feasibility of the PA maintenance intervention prototype

## Phase 1: Objective (i) Synthesis of PA maintenance theory and evidence

We will bring together theories for PA maintenance from key papers
^
20,
34–
37
^, existing scientific evidence (see below for more detail), best practice recommendations for PA including guidelines from the World Health Organisation
^
5
^, the UK Chief Medical Officers
^
38
^, Irish PA guidelines
^
39
^, best practice recommendations for PA related health behaviour change
^
40,
41
^ and PA clinical guidelines for arthritis
^
14,
42,
43
^.

The synthesis will use a programme theory approach to establish an explicit logic model of why the intervention should work, and contextual influences on this
^
30
^. This approach will allow us to define the theoretical and practical processes and potential mechanisms that lead to PA maintenance. It will also allow for the identification of the commonalities across the arthritis conditions to co-develop the intervention and implementation plans accordingly. For example, differences in PA capability can be addressed through tailoring, while in relation to the opportunities and motivations to maintain PA, there is likely to be overlap in the barriers/facilitators across people with different types of arthritis. We will consider the complexity of the intervention, particularly interactions between proposed components, how the intervention is proposed to fit in its wider context (with stakeholders), and its relevance for people with one or more type of arthritis. 

### Synthesis of the scientific evidence

Our team has published two reviews on digital tools to support PA maintenance
^
12,
22
^. A third key source is a comprehensive review of PA maintenance literature in older adults
^
44
^. To add to this information, a rapid review will be conducted to explore the effectiveness of non-digital interventions for PA maintenance in people with arthritis and extract potential intervention components.

### Rapid review

**
*Methods*
**

We will use rapid review methodology to accelerate the process of conducting a traditional systematic review through streamlining methods to produce more timely information
^
45
^. Rapid reviews adhere to the general steps of the systematic review process, use abbreviated methods from full systematic reviews, and are completed within shorter time periods
^
45
^.

### Data sources and searches

The search process will be accelerated by using a hybrid method to identify studies; this starts by identifying trials and qualitative data from relevant systematic reviews, supplemented by a search for randomised controlled trials (RCTs) published since the last search date of the reviews, if required. We will identify relevant reviews from those already completed by the team
^
8,
9,
12,
16,
27,
45,
46
^. These reviews will inform the rapid review and will accelerate our search process. The proposed rapid systematic review will follow the updated Preferred Reporting Items for Systematic Reviews and Meta-Analysis reporting guidelines
^
47
^. Assistance of an information specialist will be obtained to ensure a comprehensive search of electronic databases such as EMBASE, PubMed, CINaHL. Google Scholar will be searched for additional citations associated with final included studies. We will attempt to contact authors of published abstracts to request full-text versions of the study and/or study data. Reference lists of selected studies will be hand searched for additional studies.

Eligibility criteria are outlined using the PICOS framework
^
48
^:

P (Population) = Adults living with osteoarthritis, RA (plus other forms of arthritis to be agreed)

I (Intervention) =, non-digital PA maintenance intervention (Maintenance defined as at least 3-months after the end of the intervention)

C (Comparison) = any intervention or non-treatment control

O (Outcome) = PA measure (device based, participant report)

S (Study) = randomised controlled trials

### Study selection

Two reviewers will independently screen the titles and abstracts, and then papers that fulfil the eligibility requirements will be read in full and their suitability for inclusion will be independently decided, with disagreements resolved by a third author, if required. Results will be transferred into the Covidence software (
https://www.covidence.org)
^
49
^, for title/abstract screening.

### Data extraction and quality assessment

Study details and data will be extracted using a customised form. Theoretical information and intervention details including approaches, dose etc., will be extracted. Qualitative data will be extracted to understand people's experiences of receiving the intervention and barriers and enablers to consider in our future intervention. Risk of bias will be assessed independently by two reviewers with disagreements resolved by a third author, if required. Risk of bias will be used to weight the evidence in a subsequent meta-analysis.

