### Data synthesis and analysis

Where appropriate a meta-analysis (quantitative data) or meta-synthesis (qualitative data) will be conducted. The meta-analysis will investigate the effectiveness of non-digital interventions for PA maintenance in people with arthritis. Where such synthesis is not possible, a narrative synthesis will be conducted.

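### The rapid review commits to weighting its meta-analysis by risk of bias, so the pooled effect depends on an arbitrary score and keeps part of the bias

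*Protocol article*

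**What the plan says.** In Phase 1, under Data extraction and quality assessment, the protocol first describes how the judgement is made: "Risk of bias will be assessed independently by two reviewers with disagreements resolved by a third author, if required". It then says what the judgement is for: "Risk of bias will be used to weight the evidence in a subsequent meta-analysis".

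Under Data synthesis and analysis, pooling is conditional: "Where appropriate a meta-analysis (quantitative data) or meta-synthesis (qualitative data) will be conducted". Its purpose is quantitative: "The meta-analysis will investigate the effectiveness of non-digital interventions for PA maintenance in people with arthritis". There is a fallback: "Where such synthesis is not possible, a narrative synthesis will be conducted". The eligibility list under Data sources and searches restricts the trials to one design: "S (Study) = randomised controlled trials".

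The article names no risk-of-bias tool, no mapping from judgement to weight, no pooling model and no standard error formula. The weighting sentence is its only statement on how trials will be weighted, and nothing elsewhere qualifies or replaces it.

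**The concern.** The objection is to what the sentence prescribes, not to detail that a condensed article leaves out. Weights in a meta-analysis normally follow precision. A risk-of-bias category ranks trials by how far they can be trusted, but it does not say how large the bias is or which way it points. Using it as a weight has two unavoidable consequences and one conditional one.

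1. Somebody must choose numbers for the categories, and the pooled effect moves with that choice.
2. A biased trial with a positive weight still contributes its bias, so the bias is diluted but not removed, unless biases happen to cancel.
3. The weights no longer equal inverse variances, so the default standard error is wrong if it is computed as though they did.

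Naming a scale in a fuller review protocol would make the first choice visible but would not give it a basis. It would leave the second problem untouched. At stake is the review's answer on whether non-digital maintenance interventions work, which is one part of the evidence behind the logic model.

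**Working it through.** The protocol gives no figure on this point, so there is nothing to reproduce. The check is the algebra of a weighted mean, applied to assumed data.

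**Formulas.** Let trial i have estimate y_i, variance v_i, bias b_i and risk-of-bias score q_i, with weight w_i = q_i / v_i (add the between-trial variance to v_i for random effects).

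- Pooled estimate = Σ w_i y_i / Σ w_i
- Residual bias = Σ w_i b_i / Σ w_i
- Valid sampling SE for fixed weights = √(Σ w_i² v_i) / Σ w_i
- Default inverse-variance SE = 1 / √(Σ w_i)
- Mean squared error (MSE) = residual bias² + valid SE²

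**Illustration A (all inputs assumed).** Six trials, each with variance 0.04; two each at low, some and high risk; true SMD 0.20; bias 0, 0.15 and 0.30 respectively.

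Worked row, scores 1/0.5/0.25:

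- Σq = 2 × 1.75 = 3.5.
- Bias = 2 × (0.5 × 0.15 + 0.25 × 0.30) / 3.5 = 0.30 / 3.5 = 0.086, so the estimate is 0.286.
- Valid SE = √(0.04 × 2 × (1 + 0.25 + 0.0625)) / 3.5 = √0.105 / 3.5 = 0.093.
- Default SE = 1 / √(3.5 / 0.04) = 0.107.
- MSE = 0.0073 + 0.0086 = 0.016.

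| Scores low/some/high | Pooled SMD | Residual bias | Valid SE | Default SE | Default/valid | MSE |
|---|---|---|---|---|---|---|
| 1/1/1 (inverse variance) | 0.350 | 0.150 | 0.082 | 0.082 | 1.00 | 0.029 |
| 1/0.75/0.5 | 0.317 | 0.117 | 0.085 | 0.094 | 1.114 | 0.021 |
| 3/2/1 | 0.300 | 0.100 | 0.088 | 0.058 | 0.655 | 0.018 |
| 1/0.5/0.25 | 0.286 | 0.086 | 0.093 | 0.107 | 1.155 | 0.016 |
| 1/0/0 (low risk only) | 0.200 | 0 | 0.141 | 0.141 | 1.00 | 0.020 |

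**Illustration B (different assumed inputs).** Six trials with variances 0.04, 0.03, 0.05, 0.02, 0.03 and 0.04, paired by risk category in that order; true SMD 0.10; the same biases; no heterogeneity.

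- Scores 1/0.75/0.5, 3/2/1, 1/0.5/0.25 and 1/0.5/0.1 give pooled SMDs of 0.219, 0.203, 0.189 and 0.171.
- Subtracting 0.10 leaves residual biases of 0.119, 0.103, 0.089 and 0.071, against 0.150 with inverse-variance weights.
- A between-trial variance of 0.02 changes these little (0.217, 0.201, 0.187 and 0.167).

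**Standard error.** In B, multiplying the scores 1/0.5/0.1 by ten leaves the estimate (0.171) and the valid SE (0.088) unchanged. The default SE falls from 0.100 to 0.032. Coverage of a nominal 95% interval, ignoring bias, goes from 97.4% to 52.0%. So the default formula depends even on the units of the score. The valid formula does not, though its SE in B (0.076 to 0.088 over the four scales) exceeds the inverse-variance SE of 0.073.

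**The case against.** **Weighting reduces bias in the example, and inverse variance alone does worst.** This stands. In illustration A the all-trials inverse-variance estimate is 0.350 against a truth of 0.20, with the largest MSE (0.029). All three scored versions beat it, and two of them (0.018 and 0.016) also beat the low-risk analysis (0.020). Restriction to low-risk trials is itself a 1/0/0 weighting. But the ranking depends on assumed biases that all point one way and grow with the risk category, which the judgement itself cannot reveal. The lesson is that an all-trials estimate must not stand alone; the objection does not supply a basis for any particular score.

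**The phrase may loosely mean grading the evidence.** That is possible, since it sits under quality assessment and no score is given. But it refers to weighting in a meta-analysis, where weights have a technical meaning. If grading was meant, the sentence still needs rewording.

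**The pooled estimate may never exist and settles little.** This largely stands. Pooling is conditional, with narrative synthesis as the fallback. The logic model draws on theory, guidelines and other evidence. Phase 3 triangulates Phases 1 and 2, applies several criteria of which effectiveness is one, and puts options to workshops. A reader might infer that the pooled effect selects the intervention components; no section says so.

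**Two further inferences are not supported.** A reader might conclude that the review's standard error will be wrong. The protocol gives no formula, and a valid one exists for fixed weights, so that error is conditional. A reader might also take "C (Comparison) = any intervention or non-treatment control" to mean that active and untreated comparators will be pooled together. That line is an eligibility criterion, not a pooling rule, and how comparisons are grouped can be left to the full review protocol.

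**Conclusion.** The point holds as a should-fix. The protocol commits to a weighting rule that has no principled scale and that leaves bias in the pooled estimate. Under the assumed inputs, the choice among plausible scores moves the pooled SMD from 0.286 to 0.317 (illustration A) or from 0.171 to 0.219 (illustration B). Residual bias is 0.086 to 0.117 in A and 0.071 to 0.119 in B. These sizes rest wholly on assumed trial numbers, variances and biases. The dependence on the score and the persistence of bias follow from the algebra, apart from chance cancellation.

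The standard error fails only if the scored weights are put into the default formula; it would then be about 15% too large or 35% too small for the 1/0.5/0.25 and 3/2/1 scales in A. Even the valid sampling SE takes no account of residual bias or of uncertainty in the score.

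The reach is narrow: the rapid review's effectiveness estimate, if one is produced. Phase 4 is descriptive and mainly qualitative and does not use it.

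**What to change.** Replace the weighting sentence under Data extraction and quality assessment with:

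*Trials will be pooled by inverse-variance random-effects meta-analysis. Risk of bias will not enter the weights; a pre-specified analysis restricted to low-risk trials (or a subgroup comparison by risk category) will be reported alongside the all-trials estimate with equal prominence, and risk of bias will inform the certainty rating and the conclusion.*

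Equal prominence matters because, if biases run in one direction, the all-trials estimate can be the most biased of the options.

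The cost is a change of wording and one extra analysis, with no new data. The drawback is precision: the low-risk analysis uses fewer trials and has a wider confidence interval (SE 0.141 against 0.082 in illustration A, and 0.131 against 0.073 in B).

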### Data synthesis and analysis

Where appropriate a meta-analysis (quantitative data) or meta-synthesis (qualitative data) will be conducted. The meta-analysis will investigate the effectiveness of non-digital interventions for PA maintenance in people with arthritis. Where such synthesis is not possible, a narrative synthesis will be conducted.

## Phase 2: Observation and qualitative study

Observational Analysis: Objective (ii) Identify facilitators/deficits in supervised exercise classes to maintain PA.

### Methods

We will conduct an observational analysis of a physiotherapy led, structured exercise programme for those living with arthritis, to better understand what behaviour change components are being used that might support PA maintenance. This will be done in three steps.

1) We know that physiotherapists will be trained in advance of delivering the exercise programmes. We will review the training materials for behaviour change components related to PA.2) We will then map these behaviour change components to The Behaviour Change Technique Taxonomy (BCTT v1)
^
50
^.3) We will then undertake a direct face-to-face observational analysis of the delivery of the exercise classes, to explore which BCTs are used to support PA maintenance. A detailed checklist (informed by the evidence synthesis in part one and the review of the training materials) will be completed during each session by a member of the research team. The classes will also be audio-record classes to allow for further post observation analysis of the behavioural components for example the communication style and behaviour change techniques delivered by the class leader. Any supporting materials used by the delivering physiotherapist during the classes will also be reviewed for presence of BCTs.

